### Secondary objectives

#### Clinical

- To assess the impact of impregnated school uniforms on the number of febrile episodes during the study period (compared to the control group)
- To assess the impact of impregnated school uniforms on school absenteeism (number of days lost because of febrile illness)
- To measure the protective herd effect (halo effect) on dengue incidence in children without impregnated clothes
- To assess the safety of impregnated school uniforms in children

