### Sample size

Sample size for the trial will take into account likely levels of dengue incidence, as well as the considerable wide-area variation in transmission from season to season, and local area (i.e., per school) variation [31]. Such large potential variations are unpredictable and difficult to quantify. The advantage of the crossover school-randomised design – which can be interpreted as a cluster-randomised design in relation to individuals – is that if there are particular factors driving local area variation from year to year (such as mosquito breeding sites close to schools), those sources of variation will, to some extent, be controlled by the crossover design. This design efficiency is a considerable advantage, notwithstanding the relatively large design effect that needs to be

applied to the overall sample size in recognition of the cluster randomisation and the considerable uncertainties around wide-area incidence rates from year to year.

In view of the probable large size of these variations and their inherent uncertainty, a design factor of 3 is used.

A design factor greater than unity is justified because of the school clustering effect. Unfortunately, because of the paucity of knowledge of dengue epidemiology, both in terms of year-on-year variation and its determinants in Thailand in general, and compounded by possible local variations in dengue that might occur between school locations, it is impossible to make detailed calculations of the required design effect. The choice of 3 as the design effect was therefore adopted as a conservative estimate in the absence of being able to make any better estimate.

The basic assumptions underlying the sample size for the trial are an incidence rate (symptomatic plus asymptomatic) of an average of 5% during a transmission season [32], i.e. 10% over two seasons; an aim of halving incidence by using impregnated uniforms (since any smaller effect would not be of policy interest) and a dropout rate (children leaving the school, etc.) of 20%.

According to Schouten and Kester [33], the overall sample size for a non-clustered crossover design can be calculated as

$$2n = \frac{[z_1 - \alpha/2\sqrt{\pi_A(1 - \pi_B) + \pi_B(1 - \pi_A)} + z_1 - \beta\sqrt{\pi_A(1 - \pi_A) + \pi_B(1 - \pi_B)}]^2}{(\pi_A - \pi_B)^2}$$

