For comparing a 10% incidence with 5%, this amounts to an overall sample size of 508 (90% power,  $p = 0.05$ ). Increasing this figure by 20% to allow for dropout takes this to 610, and allowing for 10% of children to become infected and take no further part in the trial takes this to 670. A design effect of 3 then takes the total sample size to 2,012 (i.e., 1,006 in each study arm).

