### Analytical plan

The primary endpoint is a comparison of the incidence rates of laboratory-confirmed dengue infections per person-time exposed up to failure (i.e. dengue infection) or censoring (i.e. moving away) between the intervention and control groups.

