### Safety considerations

There are no apparent risks to the safety of individuals or communities in this study. Due to its low toxicity and long-lasting efficacy, permethrin is one of the most commonly used insecticides in impregnated clothing. Low irritancy and odour also add to the popularity of permethrin-impregnated clothing [19]. Permethrin-treated uniforms have been fully evaluated by multiple governments for use in military uniforms, for example in the US, Germany and France [21,36]. Even though there is some absorption of the permethrin through the skin, the amount absorbed is well below the acceptable daily intake, and health side effects are not expected [13,37,38]. Insect Shield has met all health requirements for approval by the United States Environmental Protection Agency (USEPA) and has maintained these health standards since 2006 (Insect Shield USEPA, 2009). They are approved for vector control, and the products will be

used in compliance with their recommended use and guidelines.

Teachers will document any skin irritations initially every 2 weeks, then every 4 weeks during the study period. Should skin irritations occur, the students will be sent to the study medical clinics for further documentation by trained personnel. In the case that a participant develops a serious adverse event (SAE) during the course of the study, this will be captured in the case report form. In case of an SAE, the study physician will record and manage the SAE in accordance with Good Clinical Practice (GCP). Excessive clustering of SAE by school will be reported to the study's Data Monitoring and Safety Committee (IDMC). A determination by the IDMC that there is a potential harm to participants or the environment caused by the interventions will result in discontinuation of the study.

If an individual wants to terminate his/her participation, no further follow-up will be performed. In the case of a study child leaving during year 1, they will be replaced in year 2 of the study (May-June 2013). There will be no replacement during the surveillance period either year. If a school opts out of the study before July in either year, replacement by a neighbouring school will be considered.

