### Ethical considerations

This study is conducted in accordance with the principles set forth in the International Conference on Harmonization Tripartite Guideline of Good Clinical Practice and the Declaration of Helsinki. The study was approved by the Thai Ethics Review Board. Using a crossover, school-randomised design means that every individual will be equally exposed to the risks of dengue infection and to possible benefits of the intervention, taken over the entire trial period. Serious adverse effects of wearing the impregnated clothes will be reported to the Ethics Review Board within 24 h.

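### Removing children once infected makes exit depend on the outcome: it contradicts the equal-exposure claim and truncates secondary and safety follow-up, but hardly touches the primary comparison

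*Protocol*

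**What the plan says.** The Protocol's Sample size section starts from a formula introduced with the words "the overall sample size for a non-clustered crossover design can be calculated as". Its result is given as "For comparing a 10% incidence with 5%, this amounts to an overall sample size of 508 (90% power"), on the basis of "an incidence rate (symptomatic plus asymptomatic) of an average of 5% during a transmission season [32], i.e. 10% over two seasons". This base is raised by 20% for dropout, to 610. It is raised again, to 670, by "allowing for 10% of children to become infected and take no further part in the trial". A design effect of 3 then gives 2,012, or 1,006 per sequence.

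Four other places bear on what happens to an infected child:

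- Analytical plan: the primary endpoint compares incidence rates "per person-time exposed up to failure (i.e. dengue infection) or censoring (i.e. moving away").
- Safety considerations: "In the case of a study child leaving during year 1, they will be replaced in year 2 of the study". It does not say whether an infected child counts as leaving.
- Ethical considerations: over the whole trial, "every individual will be equally exposed to the risks of dengue infection and to possible benefits of the intervention".
- The clinical part of the secondary objectives lists this aim: "To assess the impact of impregnated school uniforms on the number of febrile episodes during the study period (compared to the control group"), together with school absenteeism and safety.

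The Design section randomises and crosses over schools, not children.

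**The concern.** The removal clause appears as a sample-size adjustment, but it describes conduct: an infected child is out of the trial. Infection is the outcome the uniforms are meant to change, so exit depends on the outcome and, if the uniforms work, on the allocated condition. The 1.10 multiplier treats it as if it were random loss.

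Three things are at stake. First, the sections disagree: a control-first child infected in season 1 never reaches the treated season, so exposure to the possible benefit is not equal for every individual. Second, the formula takes its efficiency from each child giving one outcome under each condition, and a child removed after season 1 gives only one. Third, febrile episodes, absenteeism and safety do not end at a first dengue infection. Stopping observation there loses more of the treated season in control-first schools than of the control season in treated-first schools.

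**Working it through.** **The plan's own figure.** Inputs from the Sample size section: πA = 0.10, πB = 0.05, two-sided 0.05, 90% power. The printed formula gives (1.960 × √0.14 + 1.282 × √0.1375)² / 0.05² = 584.3, that is 585 and not 508. The later steps do follow from 508: 508 × 1.2 × 1.1 × 3 = 2,012. The 508 is a separate matter; it is used below only because the plan uses it.

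**Reliance on two outcomes per child.** A parallel comparison of the same rates needs 582 per arm, 1,164 in all. The crossover formula needs about 584 in all. The halving comes from each child supplying two outcomes.

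**Differential exit before season 2**, with 1,006 children per sequence:

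| Risk per season, control / treated | Control-first leave | Treated-first leave | Mean share infected in season 1 |
|---|---|---|---|
| 10% / 5% | 1,006 × 0.10 ≈ 101 | 1,006 × 0.05 ≈ 50 | 7.5% |
| 5% / 2.5% | 1,006 × 0.05 ≈ 50 | 1,006 × 0.025 ≈ 25 | 3.75% |

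The second row is shown because the plan's 10% is a two-season figure, while each child spends one season in each condition.

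**Bias in the primary comparison.** The Protocol gives no measure of variation in risk between children, so a gamma frailty with variance θ from 0 to 4 is assumed. Survival is S(H) = (1 + θH)^(−1/θ), with hazards per season hC = 0.10 and hT = 0.05.

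- Season 1 risks: 1 − S(hC) for control and 1 − S(hT) for treated.
- Season 2 risks among children still at risk: 1 − S(hC + hT)/S(hT) for control and 1 − S(hC + hT)/S(hC) for treated.
- Pooled: events over children at risk, both seasons together.

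Worked at θ = 4: S(0.05) = 0.9554, S(0.10) = 0.9193, S(0.15) = 0.8891. Season 1 is 0.0446 / 0.0807 = 0.552. Season 2 is 0.0328 / 0.0694 = 0.473. Pooled treated risk is (0.0446 + 0.9193 × 0.0328) / 1.9193 = 0.0389; pooled control risk is (0.0807 + 0.9554 × 0.0694) / 1.9554 = 0.0752; the ratio is 0.518.

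| θ | Season 1 ratio | Season 2 ratio | Pooled ratio |
|---|---|---|---|
| 0 | 0.512 | 0.512 | 0.512 |
| 1 | 0.524 | 0.500 | 0.513 |
| 4 | 0.552 | 0.473 | 0.518 |

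At hazards 0.05/0.025 the pooled ratio is 0.506 to 0.508. Holding the control risk at exactly 10% instead gives 0.513 to 0.525. The two seasons shift in opposite directions and nearly cancel.

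**Power**, at 10% versus 5%, ignoring clustering, with n children per sequence. The sum of the two seasons' risk differences is 0.10.

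- Both seasons observed in all 508 (n = 254): variance 2 × (0.14 − 0.0025)/254 = 0.001083; z = 0.10/0.0329 = 3.04; power about 86%.
- Removal, season-stratified first infection, 508: variance (0.09 + 0.0475 + 0.0475/0.90 + 0.09/0.95)/254 = 0.001122; z = 2.99; power about 85%.
- Removal with the 10% allowance, 508 × 1.10 = 559 (n = 279.5): variance 0.2850/279.5 = 0.001020; z = 3.13; power about 88%.

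Simulation of 40,000 trials per case gives 86.7%, 85.3% and (at 558) 88.5%. Removal costs about 1 point, and the allowance more than restores it.

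**Type I error.** With no effect, both sequences lose the same expected share after season 1, so depletion creates no difference.

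**The case against.** The strongest defence is that the clause occurs only in a sample-size sentence. The section on determining new infections keeps surveillance of febrile episodes going throughout the study period, and the leaving rules under Safety considerations concern withdrawal and departure, not infection. Infections found only by paired IgG at the end of the season cannot shorten season 1 follow-up. Every school still crosses over. The 10% allowance also exceeds the 7.5% mean season 1 infection implied by the plan's rates. All of this stands and limits the weight of the point. It does not remove the contradiction with the equal-exposure statement, and the Protocol nowhere says that infected children remain under follow-up.

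A reader might infer three stronger things that the documents do not support:

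- That depletion biases the trial in favour of the uniforms. The season 2 ratio does fall, but the Analytical plan compares conditions over all person-time, and the pooled ratio moves by less than 0.01, toward the null. A season 2 ratio as low as 0.43 comes from applying the hazard multiplier at the start of the season, (1 + 4 × 0.05)/(1 + 4 × 0.10) = 0.857, to 0.50. Over the whole season the same model gives 0.473.
- That half the information is lost. Of 508 × (0.10 × 0.95 + 0.05 × 0.90) = 71 expected discordant children, about 36 remain if season 1 cases are discarded, and simulated power falls to 54.7%. That requires an analysis restricted to children with both seasons, which the Protocol does not plan. Under its endpoint, season 1 infections are counted events.
- That keeping these children raises power to 88.7% and makes the allowance unnecessary. That figure keeps 2,012 children (2,012/3.6 = 559). Deleting the allowance gives 508 × 1.2 × 3 = 1,829 and no gain, and recently infected children may add few events.

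**Conclusion.** The point holds as a conflict between sections and as an avoidable outcome-dependent exit. The contradiction between Sample size and Ethical considerations follows from the text alone. The two-to-one exit (about 101 against 50, or 50 against 25) rests on the planned halving and on the clause being applied as written. The differential truncation of febrile episodes, absenteeism and safety rests on the same literal reading; its effect on those outcomes cannot be sized from the Protocol.

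For the primary comparison the effect is small: a pooled ratio of 0.512 to 0.518 at 10%/5%, about 1 point of power, an allowance that covers it, and no effect on type I error. These results assume gamma frailty with variance 0 to 4, a first-infection analysis stratified by season with at-risk denominators, and no clustering. The Protocol does not support a claim of material bias or of serious power loss from this clause.

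**What to change.** In the Sample size section, replace the removal clause with a statement that children infected in season 1 stay enrolled in their school's allocated condition and under surveillance through season 2. Then:

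- Count these children in full for febrile episodes, absenteeism and safety.
- Keep first infection as the primary analysis, stratified by season with at-risk denominators, and report second-season infections in these children as a sensitivity analysis. The detail can go in the statistical analysis plan.
- Reconcile the sections. Sample size should say that the paired formula is an approximation when follow-up for the primary endpoint ends at infection. The Analytical plan should say that infection ends primary person-time but not participation. Safety considerations should say whether infected children are ever replaced. Ethical considerations should then match the rule.
- Leave the 10% allowance in place and claim no power gain on this ground.

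The cost is wording plus continued sampling and surveillance of a few percent of children (3.75% to 7.5% on the plan's rates), who may add few further events.

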#### Determining new dengue infections during the study period

Blood samples will be collected via venipuncture (2 ml) or finger prick (<0.2ml) from all study subjects at the beginning of the school term (June 2012) and at the end of the first study period (November 2012). Dengue IgG ELISA (with titres) will be measured at the Center of Excellence for Vectors and Vector-Borne Diseases (CVVD), Faculty of Science, Mahidol University at Salaya. The paired serum samples from each volunteer will be screened quantitatively for anti-dengue IgG antibodies by ELISA using a standardised protocol and reagents.

Passive and active surveillance for dengue and febrile episodes will be maintained throughout the study period (school term).

The parents of any child treated for a febrile episode during the study period will be asked to bring their child to the nearest health facility if the child does not show improvement within 48 h. When such study subjects report to a health facility, government nurses or doctors will treat the child following national guidelines and inform the study nurses or local public health officers stationed in the study area. Blood samples for dengue IgM and IgG and dengue PCR will be taken if there is a fever > 37.5°C. In case the health centre has no facilities for taking blood, the child will be advised to go to a centre with such facilities. The blood samples will be sent to a specified laboratory centre in Bangkok.

To enhance passive surveillance, we will also undertake active surveillance of febrile episodes. During the school term, field assistants will daily check from the school records for children who have been reported as absent for 2 days. The caretakers of those children will be contacted to find out about the reason for absenteeism. For those children who are reported to be absent because of a febrile illness, a blood sample will be taken within 4 weeks after onset of illness to check for dengue IgM. Furthermore, any laboratory data and clinical information will be collected directly from the health centre

in case the child has gone to such a health centre or hospital.

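### Adverse events are actively sought only as skin irritation, and the absence call that already asks every caretaker for the reason has a stated follow-up only for fever, so non-febrile, non-skin events and admissions are likely to be under-detected

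*Protocol*

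**What the plan says.** The Protocol lists among its secondary clinical objectives: "To assess the safety of impregnated school uniforms in children".

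The Safety considerations section schedules one search for harm: teachers note skin irritation, at first every two weeks and later every four, and affected pupils go to the study clinics. If an SAE develops, "this will be captured in the case report form". The study physician records and manages it, and excessive clustering of SAEs by school goes to the monitoring committee (IDMC). The Ethical considerations section adds a 24 h limit for reporting serious adverse effects of the clothing to the ethics board.

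A separate contact is set up to find dengue, in the section on determining new infections. During term, "field assistants will daily check from the school records for children who have been reported as absent for 2 days". Then: "The caretakers of those children will be contacted to find out about the reason for absenteeism". The follow-up given is: "For those children who are reported to be absent because of a febrile illness, a blood sample will be taken within 4 weeks". The stated purpose is fever: "we will also undertake active surveillance of febrile episodes". A last sentence covers children who attended a health centre or hospital: "Furthermore, any laboratory data and clinical information will be collected directly from the health centre".

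**The concern.** The trial has a daily, school-wide contact that hears why a child is away, and a separate safety system that does not mention it. The safety system depends on teachers, who do not see absent pupils, and on SAEs becoming known by a route that is not described. A child admitted without fever, or kept at home with a rash or a respiratory complaint, is the child the absence call would reach. The plan names no place for that answer to be recorded as a possible adverse event.

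Two things depend on it. A report of no safety signal would be hard to interpret if events were not looked for. The IDMC rule on clustering by school also works only on SAEs that reach the study, and school is the unit of randomisation. How adverse events are found in the field is a matter of trial conduct, which this document sets, so a separate analysis plan would not answer the point.

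**Working it through.** The Protocol states no figure on this point, so there is none to reproduce. The check is to follow each kind of event through the stated routes.

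1. **Febrile illness.** Covered by passive and active surveillance. Febrile episodes and days absent with fever are secondary outcomes, and the Economic analysis section adds a questionnaire on symptoms, duration and care. No gap of note.
2. **Skin irritation in a child at school.** Covered by the teacher notes and referral to the study clinics.
3. **Skin reaction that keeps the child at home.** The teacher may not see it. After two days of absence the caretaker is asked the reason, but no recording step is stated for a non-febrile answer.
4. **Non-febrile admission in term, with two or more school days missed.** The absence call should hear of it. No step is stated that takes the answer to the case report form or the study physician.
5. **Non-febrile, non-skin complaint without a two-day absence.** No route of detection is stated.
6. **Any non-febrile event outside term.** The absence check does not run, and no other route is stated.

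The gap is rows 3 to 6. The absence call could supply rows 3 and 4, and the part of other non-febrile illness that leads to a two-day absence. It cannot supply rows 5 and 6.

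**Illustration, not an estimate.** Let r be the true SAE risk per child, d the share detected, and n = 1,006 children per arm (Sample size section). Children are treated as independent. The chance of seeing at least one SAE in an arm is 1 − (1 − r·d)^n. The values of r and d are assumptions, since the Protocol gives neither.

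| Assumed r | d = 1 | d = 0.5 | d = 0.25 |
|---|---|---|---|
| 1 per 1,000 | 63% | 40% | 22% |
| 2 per 1,000 | 87% | 63% | 40% |
| 5 per 1,000 | 99% | 92% | 72% |

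For example, r = 0.002 and d = 0.5 gives 1 − (1 − 0.001)^1,006 = 0.63, with 1,006 × 0.001 = 1.0 event expected instead of 2.0. At low event rates, incomplete detection can decide whether anything is seen at all.

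**The case against.** Several points on the other side are fair.

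- **Silence is not discarding.** A reader might infer that non-febrile answers are thrown away. The Protocol does not say so. That section is about finding dengue and names the follow-up that serves that purpose, while the safety section says SAEs will be recorded. A field assistant told of an admission might well pass it on. What stands is that this is left to chance.
- **There is a hospital-data sentence.** It could be read as covering every absent child. It follows directly on the fever sentence, however, and states no adverse-event purpose and no link to SAE handling.
- **Other events are collected.** A reader might infer that nothing outside skin and SAEs is recorded. That is wrong: febrile illness is collected in detail. The gap is confined to non-febrile, non-skin events and non-febrile admissions.
- **The focus on skin has a reason.** The sentence that begins "Even though there is some absorption of the permethrin through the skin" goes on to say that uptake is well within the acceptable intake and that no side effects are expected. Children with eczema or severe skin disease are also excluded. This supports skin as the main focus, but an expectation of no side effects is what a safety objective should be able to test.
- **No detection share can be derived.** It is tempting to compute one from the interval between teacher notes. That would assume a one-day snapshot, whereas the notes may cover everything seen since the last entry. It would also describe children at school, whom the absence call does not reach.
- **The groups are treated alike.** With blinding intact, under-detection should be similar in both groups. This is right and limits the harm to lost sensitivity.

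**Conclusion.** The point holds as a minor one. The Protocol schedules a search only for skin irritation and describes the handling of SAEs without saying how they come to notice. It leaves a contact it already makes with caretakers unused for safety. Non-febrile, non-skin events and non-febrile admissions are therefore likely to be under-detected, which weakens the answer to the safety objective and the SAE count on which the IDMC relies.

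The size cannot be derived from the documents. The conclusion rests on reading the fever follow-up and the hospital-data sentence as they stand, with no further operating procedure at hand. It does not support a claim that SAEs are ignored or that the comparison between groups is biased.

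**What to change.** Extend the existing absence contact as follows.

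- Use one script in all schools and both seasons. Record on the case report form the reason for absence whatever it is, including any hospital admission and any skin, respiratory or other new complaint.
- Pass every admission to the study physician for SAE assessment, on a timeline consistent with the 24 h reporting in the Ethical considerations section. An admission is a trigger for assessment and is not automatically an SAE.
- Tabulate laboratory-confirmed dengue admissions separately as outcomes. Dengue is expected to vary between schools, so counting these admissions as SAEs could by itself produce the school clustering that goes to the IDMC.
- Report the events by allocated group beside the teachers' skin records.

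The cost is a few questions added to a contact already made by existing field staff. Some unrelated events will be recorded, in similar numbers in both groups if blinding holds. The check covers only term time and absences of two days, so complaints without absence and events in holidays remain outside it, and the report should say so.
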